### Model of service

The WACHS CC began operations in 2012 as the Emergency Telehealth Service (ETS), a virtual health solution to support diagnosing, treating, and managing patients in local regions.^
26
^ The ‘Command Centre’ was officially launched in 2019 from recommendations of the Department of Health, Western Australia's Sustainable Health Review.^
27
^ A suite of services have since been implemented, beginning with the Inpatient Telehealth Service, and Mental Health Emergency Telehealth Service, and more recently, the Midwifery and Obstetrics Emergency Telehealth Service,^
28
^ and the Palliative Care Afterhours Telehealth Service.^29,30^ While these services differ in their functionality and purpose, they all deliver provider-to-provider specialist and clinical advice via virtual means, supporting the front-line clinicians caring for patients in rural and remote areas. The CC's Clinical services aims are as follows:
Facilitate appropriate decision making in the treatment and care of country patients.Support our place-based workforce by providing guidance, advice, and access to specialist knowledge to help provide the best care possible for rural and remote patients.Build a collaborative, integrated workforce, blending place-, and remote-based clinicians to deliver care to the highest possible quality and safety standard and in the most culturally appropriate way.Unlike other virtual or telehealth care, which is often between the patient and provider, these services are usually between the rural and remote front-line provider, with the patient present, and the specialist provider. The suite of CC services is enabled in 87 of the 103 health facilities.

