### Design

The research will use an explanatory sequential mixed methods approach^
31
^ across multiple phases, displayed in Figure 2. This type of design is suitable for a real-life complex healthcare service, allowing greater understanding from multi-faceted sources.^
32
^ The CC is an active and dynamic set of healthcare services that have been implemented for varying lengths of time, and are operating within a larger public health system. The study will begin with quantitative data collection and analyses, followed by a qualitative phase used to explain and better understand the quantitative results.^
31
^ This will be followed by an interpretative phase where data are triangulated and synthesised to develop evidence-based recommendations for implementation improvements.

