### Proposed phases, data collection, and analyses

There are three phases for this research: CC service data analyses; a survey and semi-structured interviews; and an interpretation and testing of results phase. These are intended to answer the research questions outlined in Table 1, mapped to research objectives. Data to be collected and analysed are described in Table 2, mapped to the expanded reach, effectiveness, adoption, implementation, maintenance (RE-AIM), and implementation outcomes framework (IOF) framework definitions defined by Reilly et al.^
33
^

**Table 1. table1-20552076241242790:** Research questions mapped to objectives.

Objective	Research questions
1. Evaluate the implementation of rural provider-to-provider telehealth services in country WA.	What is the reach and adoption of Command Centre services over time? What are the differences in reach and adoption across regions, sites, and health facility types? What are the differences in characteristics of patients involved in an episode of care from Command Centre services? What proportion of WACHS hospital presentations are referred to the Command Centre?
2. Explore factors associated with the differential use of rural provider-to-provider telehealth.	What are the differing behaviours, attitudes, and perceptions front-line providers have for Command Centre services? Is there a difference in the characteristics/demographics of providers who use Command Centre services? What do providers see as the benefit and value of the Command Centre services? What are the perceived risks to the place-based provider in using Command Centre services? What are the main reasons providers do not use Command Centre services? Did environmental or policy changes (system/outer context factors) influence service reach and adoption?
3. Triangulate and synthesise results to develop evidence-based recommendations to improve the implementation and sustainment of rural provider-to-provider telehealth.	What are the core components of Command Centre services? What adaptations have been made to Command Centre services to better suit local contexts? What factors potentially influence the sustainment of the Command Centre? How can the Command Centre services be improved to better integrate virtual healthcare and support the place-based workforce?

WACHS: Western Australia Country Health Service; WA: Western Australia.

**Table 2. table2-20552076241242790:** Data measures guided by the expanded RE-AIM and IOF.^
33
^

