#### Phase 1: command centre service data analyses

Data from each of the CC services will be collated from the date of implementation, or when useful data collection commenced, to the date of data extraction. These vary based on the service, with dates to be outlined on analyses.

Variables to be collected and analysed for each service are framed around the evaluation of implementation status and implementation outcomes, integral and proceeding to successful service and clinical outcomes.^
35
^ Service data will be collected for all ‘service contacts’ across the 103 WACHS-run health facilities, which were referred to the CC. No individual staff data are collected in the service data, therefore ‘Episode’ volume will be used to demonstrate the reach (patient level) and adoption (organisational level), as outlined in Table 2.

CC service data will be analysed via descriptive statistics including measures of frequency, percentages, central tendency, and variation. The analyses will describe each CC service, by site, by region, and by health facility type. Prior to analyses, the data will be transformed into a suitable format across the services to enable cross-tabulation across variables. The data will also be checked for missing or not applicable data or the presence of any anomalies. Inferential statistics will be used to test for analysis of variance between patient contacts (dependent variable) and the region, health establishment type, and site (Independent variables), per service.^
41
^

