^ The mixed methods design, theoretical frameworks, and a reflexive thematic analysis technique are employed throughout research design, data collection, and data analysis. These have been shown to be useful in complex healthcare settings and long-term sustainment approaches, assisting with data interpretation and reducing bias.^69,70^ Additionally, the researcher is independent of WACHS and will make this clear in the survey and interviews, while ensuring participant confidentiality.

Second, this research is focused on the perspective of the front-line providers who work with patients in rural and remote areas, and how the services can be of benefit. Although patient episode data will be captured, which outlines the extent of implementation and access status, the consumer perspective is therefore out of scope, but recommended for future research to capture a more holistic view.

Third, the suite of clinical CC services was implemented at various times and locations, with varying data collection platforms and data fields. To combat this, data will be analysed using the same data variables, allowing for comparison across services.

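### Using the same data variables does not correct for unequal time in operation, so raw patient contacts can confuse how long a site or service has run with how well it was adopted

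*Protocol article*

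**What the plan says.** The third limitation in the Discussion states that "the suite of clinical CC services was implemented at various times and locations, with varying data collection platforms and data fields". The next sentence gives the remedy: "To combat this, data will be analysed using the same data variables, allowing for comparison across services". The Design section likewise calls the Command Centre an "active and dynamic set of healthcare services that have been implemented for varying lengths of time".

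The Phase 1 section collates each service's data "from the date of implementation, or when useful data collection commenced, to the date of data extraction". It says that these dates vary by service and will be set out with the analyses. Episode volume is to stand for both reach and adoption. The description is by service, site, region and facility type. The inferential step is an analysis of variance, run separately for each service, with patient contacts as the dependent variable and region, facility type and site as factors.

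Table 2 lists the number of contacts, contacts as a proportion of all facility presentations, a classification of sites as active users based on patient volume, and reach and adoption over time. Table 1 asks "What is the reach and adoption of Command Centre services over time" and, under Objective 2, "Did environmental or policy changes (system/outer context factors) influence service reach and adoption".

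**The concern.** The limitation names two different problems, and the remedy fits only one. Harmonised variables make a contact mean the same thing in each service. They do not make the observation periods equal. The clause on when usable data began adds a second source of unequal periods, because recording may start later than the service did. Setting out the dates discloses the inequality but does not adjust for it.

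The stated dependent variable is a count, with no rate, offset, common window or time factor. If sites or regions joined a service at different dates, part of any difference in contacts reflects months open. The same applies to the active-user classification: a recently connected site may fall below a volume threshold only because it is recent. Objective 2 sets out to explain differential use, and Phase 3 builds recommendations on it. An artefact of roll-out order could therefore be taken forward as something for the survey and interviews to explain.

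**Working it through.** The plan states no figure for Phase 1, so there is none to reproduce. Its only computed design figure, the survey sample size, has no bearing here. The check compares the stated remedy with the stated problem, then illustrates the size.

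**Step 1. Problem against remedy.**

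| Problem named in the Discussion | Does using the same variables address it? | Other provision in Phase 1 |
|---|---|---|
| Differing platforms and fields | Yes | Data transformed to a common format |
| Differing start times and locations | No | Dates set out; no adjustment stated |

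**Step 2. Exposure between services (descriptive comparison).** Inputs from the Model of service section: the first service began in 2012, and "The ‘Command Centre’ was officially launched in 2019". I take 2019 as the start of a later service; separate start dates are not given. The extraction year is also not given, so I assume 2022 to 2025.

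Ratio of years open = (extraction year − 2012) / (extraction year − 2019)

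- 2022: 10 / 3 = 3.3
- 2023: 11 / 4 = 2.75
- 2024: 12 / 5 = 2.4
- 2025: 13 / 6 = 2.2

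At equal yearly rates, total contacts would differ by these factors with no difference in uptake. Shared variable definitions leave the ratio unchanged.

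**Step 3. Exposure within a service (where the test is run).** The spread of site or regional start dates is not given, so this is an illustration only. Assumptions: 87 sites (the number enabled) divided nearly evenly among 7 regions; the same true rate distribution in every region; mean 100 contacts per year with a between-site coefficient of variation of 0.5; Poisson counts; a 12-year window; regional starts spread evenly over S years; 4,000 runs. The figures are the share of runs in which a one-way analysis of variance by region rejects at 5%.

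| S (years) | Longest/shortest exposure, 12/(12 − S) | Total contacts | Contacts per year open |
|---|---|---|---|
| 0 | 1.0 | 4.8% | 4.8% |
| 1 | 1.09 | 6.3% | 5.2% |
| 2 | 1.2 | 9.1% | 4.8% |
| 4 | 1.5 | 36.4% | 4.9% |
| 6 | 2.0 | 85.8% | 4.5% |

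With totals, false differences between regions are modest for a spread of 1 or 2 years and severe at 4 or more. Dividing by time open holds the error rate near 5% throughout.

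**The case against.** The case on the other side has five parts.

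- **No test between services.** The analysis of variance is run within each service, and the reader will be told the dates. This stands. A reader might infer that services are tested against each other on confounded totals, but the plan states no such test. Comparison across services is descriptive, although the Discussion does claim that shared variables permit it.
- **No site dates.** The years 2012 and 2019 are when the first service began and when the Command Centre was launched. A reader might turn them into a 2.4-fold gap between sites, or a larger one for newer sites. The documents give no site go-live dates, so neither can be asserted. This stands.
- **A standardised measure exists.** Table 2 lists contacts as a proportion of presentations. If both cover the same period, length of exposure largely cancels. This stands in part: the matching of periods is not stated, and the proportion is not the dependent variable of the test.
- **Time and policy are not ignored.** A reader might infer that the over-time and policy questions have no analysis at all. That is too strong. Reach and adoption over time is a listed measure, Phase 2 explores contextual factors by survey and interview, and Phase 3 integrates these with service data. In an explanatory mixed-methods design, that is a legitimate qualitative route to the policy question.
- **This is a condensed article.** Time-trend models, offsets and event lists may sit in a fuller document. This stands for modelling detail. It does not rescue a sentence that offers a remedy for a problem the remedy cannot touch.

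One further caveat favours the plan. With site as a factor, an analysis of variance needs more than one value per site, so contacts may in fact be counted by period. The article does not say so. If they are, unequal length matters less, provided that periods before go-live are not entered as zeros.

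**Conclusion.** The point holds in a limited form. The Discussion sentence is wrong as written: using the same variables addresses field differences only. As stated, the Phase 1 test and the active-user classification rest on volume with no allowance for time in operation. Where go-live dates differ within a service, newer sites or regions would look like weaker adopters.

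For descriptive totals across services, the distortion is about 2.2- to 3.3-fold for a 2012 against a 2019 start. This assumes equal yearly rates and extraction in 2022 to 2025. For the within-service tests the size is unknown, because the spread of start dates is not given; the simulation shows only that it could range from slight to serious.

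The change is worth making because it is cheap and the recommendations depend on reading differential use correctly.

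**What to change.** 1. In the Phase 1 section, replace raw contacts as the dependent variable with one of three options: contacts per month of operation since site go-live, counting only months that the data cover; contacts per facility presentation over the same period, which Table 2 already lists; or contacts within a calendar window common to the sites or services compared.
2. Apply the same basis to the classification of sites as active users in Table 2.
3. Report the chosen measure by calendar period, so that the over-time question in Table 1 has a stated quantitative answer.
4. Correct the third limitation in the Discussion to say that shared variables address differences in fields, and that unequal time in operation is handled by the chosen measure.

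The cost is mainly a table of go-live dates by site and service. These should be obtainable, since the fidelity measure in Table 2 compares roll-out with the implementation plan. A common window discards some early data for that comparison. Interrupted time-series modelling of dated policy events is optional; the survey and interview route to the policy question can stand without it.
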